The primary objective of this study is to investigate the effectiveness of AMBIT for patients with SMI-PD in comparison to treatment with FACT. It is hypothesized that an AMBIT approach will be more effective in improving outcomes on a broad spectrum of life domains (e.g. leisure activities, education, housing, family, symptoms, and drug use) in patients with SMI-PD than FACT.

Furthermore, this study aims to investigate differences in treatment effects of the following secondary variables regarding personality functioning, and social- and societal functioning, mentalizing capacity, epistemic trust, and suicidality. It is hypothesized that patients in the AMBIT condition show greater improvement on a broad spectrum of outcomes, considering psychiatric symptoms, social ecology, relationship networks/qualities, and resiliencies as measured by the instruments included in the present study as discussed in the method section.

Cost-effectiveness will also be evaluated for AMBIT. It is hypothesized that AMBIT will be a more cost-effective treatment than FACT.

Lastly this study aims to investigate variables that may moderate and mediate treatment outcome. It is expected that severity of childhood trauma, and duration of illness have a moderating effect on treatment outcome, while epistemic trust and mentalizing capacity are expected to have a mediating effect on treatment outcome.

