### Participants

2.2

The study sample will consist of 160 patients with SMI-PD receiving care at GGZ Rivierduinen and GGZ Altrecht, mental health facilities in the Netherlands. 40 patients will be recruited at the FACT teams of Altrecht (FACT-ALT), 40 patients at the FACT teams of GGZ Rivierduinen (FACT-RIV), 40 patients at the AMBIT-PD teams of Altrecht (AMBIT-PD-ALT) and 40 patients at the AMBIT informed-MBT team of Rivierduinen (AMBIT-MBT-RIV). Participants will be recruited via their principal therapist in each of the participating teams when they meet inclusion criteria. Eligibility of each participant will be assessed before recruitment of a participant.

Participants are eligible if they 1) are 18 years of age or older, 2) are willing and able to give informed consent, 3) have a present diagnosis of a PD meeting DSM 5 criteria, 4) meet the criteria of SMI (5, 7, 8). This includes having a persistent psychiatric disorder that requires care and treatment, having undergone at least two years of treatment without achieving functional recovery (GAF ≤ 50), and experiencing impairment in social and/or societal functioning, such as difficulties in at least two areas of life, including financial issues, educational or occupational challenges, housing problems, relationship issues, substance abuse, or school/work difficulties. The dysfunction must be caused by or result in a psychiatric disorder, and coordinated care from professional caregivers in care networks is necessary to implement a treatment plan.

Participants are excluded from participation in this study if they 1) do not master the Dutch language, 2) are significantly under the influence of substances and are unwilling to detoxify elsewhere, or 3) if they have an intellectual impairment (IQ < 80, based on the Wechsler Adult Intelligence Scale).

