#### Sample size calculation

2.2.1

Based on previous studies reporting reductions in overall psychiatric symptoms following MBT, with effect sizes ranging from 0.59 to 1.79 (38), an *a priori* power analysis was conducted in G*Power 3.1.9.6 to determine the optimal sample size. Assuming a medium effect size (f = 0.25), a significance level of α = 0.05, and 90% power in a repeated-measures ANOVA with three measurements across three conditions, a total of 135 participants would be required to detect an existing effect. Accounting for an anticipated dropout rate of approximately 20%, a final sample size of 162 participants will be recruited to maintain sufficient power.

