#### Multilevel (mixed) model analysis

3.1.3

Multilevel (mixed) model analysis will be conducted to compare outcomes for both conditions on the OQ-45.2, with baseline scores (T0), scores after 9 months (T1), and at the end of treatment after 18 months (T2) as dependent variables and treatment (FACT or AMBIT) as independent variable. The different levels for the multilevel (mixed) model analysis will be: 1) participant, 2) measurement wave, 3) outcome measure, and 4) location of sampling. A multilevel (mixed) model analysis uses all data and contributes to power in the analysis in contrast to case wise deletion for missing data.

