#### Moderating and mediating effects

3.1.4

To analyse the moderating effect of the factor variable (i.e. severity of childhood trauma and duration of illness) on treatment outcome in both treatment conditions an ANOVA will be performed, with the moderating factors, treatment condition and their interaction term as independent variables and the OQ-45.2 scores as dependent outcomes.

A linear regression analysis will be performed to investigate a potential mediating relationship between the treatment conditions and epistemic trust and reflective functioning.

Furthermore, given potential differences across locations, an exploratory moderation analyses with location as a categorical moderator will be conducted.

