## Discussion

4

The present study aims to investigate the effectiveness and cost-effectiveness of AMBIT informed-MBT, AMBIT-PD and FACT for patients with SMI-PD, compared to existing treatment in FACT teams. Scientific research is particularly important for this population, as they experience significant distress and frequently do not receive adequate care within conventional treatment pathways. This study aims to explore differences in treatment effects on global functioning, mentalizing capacity, epistemic trust, suicidality and cost-effectiveness. Additionally, it seeks to identify mediators and moderators of treatment outcomes to better understand factors that contribute to therapeutic success.

This study design has several strengths. First, it aims to contribute to the development of AMBIT-informed care tailored to the individual needs of patients with SMI-PD. AMBIT is based on the concept that epistemic mistrust can undermine effectiveness of care and treatment, and focuses on mentalizing, an integrative approach, collaboration and network building, addressing distrust and engagement, and adaptability. Second, the current study has a controlled naturalistic longitudinal cohort design, offering the possibility to adapt treatment and circumstances to the participants included in the study in such a way that it stays close to everyday practice of care for these patients. It can therefore be considered a more ecologically valid and generalizable approach to effectiveness research in psychotherapy. Finally, to our knowledge, (cost-)effectiveness of an AMBIT-informed treatment has not yet been investigated but is important for determining which intervention may be preferred.

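### The mediation analysis in section 3.1.4 names treatment and the two mediators but no outcome, so on its plain reading it cannot test the stated mediation hypothesis

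*Protocol article*

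**What the plan says.** The aims at the end of the Introduction set out a hypothesis with three variables, in which "epistemic trust and mentalizing capacity are expected to have a mediating effect on treatment outcome". The Discussion repeats the aim: "it seeks to identify mediators and moderators of treatment outcomes to better understand factors that contribute to therapeutic success".

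Section 3.1.4 (Moderating and mediating effects) gives the analysis in one sentence: "A linear regression analysis will be performed to investigate a potential mediating relationship between the treatment conditions and epistemic trust and reflective functioning". The sentence does not say which variable is dependent, and OQ-45.2 does not appear in it.

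The moderation analysis just above it, in the same section, does name its outcome. It takes the moderators, "treatment condition and their interaction term as independent variables and the OQ-45.2 scores as dependent outcomes".

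Table 1 schedules OQ-45.2, QET (epistemic trust) and RFQ (reflective functioning) at T0, T1 and T2.

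**The concern.** Mediation is a statement about a path from treatment through an intermediate variable to an outcome. It needs evidence that treatment moves the mediator and that the mediator, given treatment, is related to outcome. The sentence in section 3.1.4 covers the first link only.

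The gap matters here because the Introduction presents restored epistemic trust and better mentalizing as the way AMBIT is thought to work, and AMBIT targets both directly. A group difference on QET or RFQ is therefore plausible whether or not those scales have any bearing on OQ-45.2. An analysis that stops at the group difference would leave the mechanism question unanswered, and its result could be misread as support for the mechanism.

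**Working it through.** **Step 1: compare the hypothesis with the analysis.**

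| Place in the protocol article | Treatment | Mediator | Outcome |
|---|---|---|---|
| Introduction, hypothesis | yes | epistemic trust, mentalizing capacity | treatment outcome |
| 3.1.4, mediation sentence | yes | epistemic trust, reflective functioning | none named |
| 3.1.4, moderation sentence | yes | not applicable | OQ-45.2 |

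**Step 2: look for the missing path elsewhere.** Section 3.1.3 is the primary model: "Multilevel (mixed) model analysis will be conducted to compare outcomes for both conditions on the OQ-45.2". Its independent variable is treatment, and it contains no mediator. Section 3.2 covers the ESM variables and the comparison of AMBIT informed-MBT with AMBIT-PD, again with no mediator. No section supplies a model of OQ-45.2 on QET or RFQ.

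**Step 3: illustrate the consequence.** The plan gives no figure to reproduce. The inputs are:

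- 80 AMBIT and 80 FACT participants, from section 2.2 (four groups of 40; "The study sample will consist of 160 patients with SMI-PD receiving care at GGZ Rivierduinen and GGZ Altrecht").
- 20% dropout, from section 2.2.1, giving 80 × 0.80 = 64 per group.
- α = 0.05, from section 2.2.1 ("a significance level of α = 0.05, and 90% power in a repeated-measures ANOVA"), taken as two-sided.
- Assumed, not in the plan: the treatment shift in the mediator (a = 0 or 0.5 SD), the mediator-to-outcome slope (b = 0 or 0.3) and a direct effect of 0.2, with unit residual SDs.

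For a regression of mediator on treatment with n per group, the test statistic is t with 2n − 2 degrees of freedom and noncentrality a·√(n/2):

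- a = 0: rejection rate 5% at any n.
- a = 0.5, n = 64: noncentrality 0.5 × √32 = 2.83, critical value 1.979 on 126 df, rejection rate 80%.
- a = 0.5, n = 80: noncentrality 0.5 × √40 = 3.16, critical value 1.975 on 158 df, rejection rate 88%.

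The slope b does not enter this calculation. A simulation of 4,000 data sets with 80 per group compares this regression with a joint test that requires both paths to be significant (treatment to mediator, and mediator to outcome adjusted for treatment):

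| a | b | True mediation? | Mediator on treatment alone | Joint test of both paths |
|---|---|---|---|---|
| 0.5 | 0 | no | 88.1% | 4.6% |
| 0.5 | 0.3 | yes | 88.0% | 84.7% |
| 0 | 0.3 | no | 5.2% | 4.9% |
| 0 | 0 | no | 5.2% | 0.3% |

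The first two rows carry the point. The treatment-to-mediator regression gives the same answer with and without mediation, while the joint test separates the two cases.

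**The case against.** The best defence is that the sentence is a loose summary of a standard analysis. Mediation implies an outcome by definition, the Introduction and Discussion both speak of treatment outcome, the neighbouring moderation sentence names OQ-45.2, and linear regression is an ordinary tool for estimating mediation paths. The sentence fixes neither the dependent variable nor the number of equations, so a conventional mediation model may be what the authors have in mind.

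Part of this stands. A reader might infer that the plan commits to regressing the mediators on treatment and nothing else, or that the team will report any group difference on QET or RFQ as mediation. The document says neither. The first is the plain reading of an incomplete sentence, and the second would be a prediction about conduct. It also stands that time order, the type of confidence interval and the number of models can be left to a fuller plan, so their absence from an article is no error.

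The defence does not remove the point. Whichever variable is taken as dependent, the sentence lists treatment and the mediators and leaves out the outcome. The sentence on moderation shows that the authors chose to name the outcome at this level of detail. If a standard mediation model is intended, the sentence misdescribes it and still needs correcting.

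The rejection rates are also open to challenge. They depend on the assumed shift, and imputation or propensity matching would change the numbers analysed. They illustrate the problem and are not separate evidence for it.

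**Conclusion.** The point holds in a limited form. The mediation analysis as described does not match the hypothesis it is meant to test, and no other section fills the gap. Taken as written, it cannot distinguish mediation from a group difference on the mediator.

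The chance of a significant result without mediation runs from about 5% to between 80% and 88%, conditional on no mediator-to-outcome effect, a shift of 0 or 0.5 SD, and 64 to 80 per group. The structural conclusion rests on none of these values, because the regression's result does not depend on the path from mediator to outcome.

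The reach is confined to the mechanism aim, which the Introduction lists last. The OQ-45.2 treatment comparison is unaffected. The correction should be made, but it does not threaten the main result.

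**What to change.** In section 3.1.4, name OQ-45.2 as the outcome and replace the single regression with two models:

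1. Mediator (QET or RFQ) on treatment, adjusted for the baseline mediator.
2. OQ-45.2 on the mediator, adjusted for treatment, baseline OQ-45.2, the baseline mediator and the confounders used in the propensity score.

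Report the indirect effect with a confidence interval. Preferably take the mediator at T1 and OQ-45.2 at T2, so that the mediator precedes the outcome. Label the result associational, since neither treatment nor mediator is randomised.

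A bootstrap interval for the product of coefficients, with one model per mediator, is a reasonable way to do this. These are suggestions, not corrections of an error.

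The cost is one paragraph. Table 1 already schedules all three instruments at every wave, so no new data are needed.

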### Secondary analyses

3.2

As for the primary analysis multilevel (mixed) models will be used for evaluation of the course of the ESM outcome variables over time. Since ESM data of each questionnaire is nested within days and again within the measurement period (T0, T1 or T2), measurements cannot be deemed independent, which requires the analysis of the data within a multilevel structure. The different levels for the multilevel (mixed) model analysis will be: 1) participant, 2) measurement wave, 3) outcome measure, and 4) location of sampling.

In order to compare within group differences (AMBIT informed-MBT vs AMBIT-PD) in the AMBIT condition on the primary outcome, multilevel (mixed) model analyses will be conducted to, with baseline scores (T0), scores after 9 months (T1), and at the end of treatment after 18 months (T2) as dependent variables and treatment (AMBIT informed-MBT and AMBIT-PD) as independent variable.

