##### AMBIT-PD

2.5.1.2

The AMBIT- PD condition is provided in five teams at Altrecht. These teams are trained in the AMBIT methodology and focus on working in a mentalized manner with patients and aim at building a mentalizing network around the patients. These teams have daily multidisciplinary meetings and every two weeks either InterVision or supervision with the team. A major difference with the AMBIT informed MBT condition is that MBT group-therapy is not mandatory in the AMBIT-PD condition. In the AMBIT informed MBT condition, therapy is individualized, meaning that whether patients receive MBT group-therapy, individual MBT and other interventions, such as, family therapy, pharmacotherapy or trauma-therapy is adjusted to the patient’s needs and wishes. Patients in these teams are treated for, on average, three to five years, but sometimes longer.

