#### Baseline differences and matching

3.1.1

Differences in baseline demographic and clinical characteristics between participants in the AMBIT informed and FACT conditions will be assessed using appropriate statistical models. For dichotomous variables, chi-square tests or Fisher’s exact tests (where applicable) will be conducted, while continuous variables will be analysed using independent samples t-tests or Mann-Whitney U tests in the case of non-normal distributions. Additionally, multivariate logistic regression (for categorical outcomes) and linear regression (for continuous outcomes) will be employed to adjust for potential confounders and assess the robustness of group differences.

The total sample of participants will be divided in different groups, based on identified clinically relevant differences in baseline demographic or clinical characteristics. Patient pairs will be matched on the smallest difference in propensity score (see below) within these groups (44).

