#### Propensity score matching

3.1.2

A propensity score is calculated, which is a statistical approach that attempts to reduce selection bias and known confounding that could be found in an estimate of treatment outcome in an observational study. A propensity score is the conditional probability that a participant in a study will be assigned to one of two treatment groups in this study, given a set of observed pre-treatment characteristics. Pre-treatment characteristics are demographic and clinical characteristics of participants (partly) determining the indication for a specific treatment, such as diagnoses or social situation. They will be included in the propensity score calculation as they may be related to treatment outcome and are therefore considered potential confounders. A linear regression analysis will be conducted to identify how pre-treatment variables relate to outcome, with pre-treatment variables as the dependent variable and each potential confounder as an independent variable. The propensity score for each participant will then be estimated using logistic regression analysis with all potential confounders as independent variables and ‘group membership’ (the condition to which the participant was assigned to) as the dependent variable. Each participant from one condition will then be matched with a participant from the other condition, based on the nearest available propensity score, pairs with a propensity score difference of 0.10 will be removed from the analysis, resulting in matched pairs that show no difference on any of the observed pre-treatment characteristics. A regression analysis will then be conducted in the matched sample with the identified confounding pre-treatment characteristics as dependent variable and the ‘group membership’ as the independent variable to reduce the effect of treatment group membership (44, 86, 87).

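### The comparison of AMBIT informed-MBT with AMBIT-PD states no case-mix adjustment, and any adjustment would be partial because each AMBIT type is delivered at one institution only

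*Protocol article*

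**What the plan says.** **The comparison (3.2 Secondary analyses).** The two AMBIT types are compared on the primary outcome by multilevel models, with "treatment (AMBIT informed-MBT and AMBIT-PD) as independent variable". The outcome side is given as "with baseline scores (T0), scores after 9 months (T1), and at the end of treatment after 18 months (T2) as dependent variables", so the baseline OQ-45.2 score is an outcome and not a covariate. No covariate, matching or weighting is named for this contrast.

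**The confounding control (3.1.1 to 3.1.3).** Baseline differences "between participants in the AMBIT informed and FACT conditions will be assessed using appropriate statistical models". The propensity score is the probability that a participant "will be assigned to one of two treatment groups in this study, given a set of observed pre-treatment characteristics", and members of one condition are matched to members of the other. The primary model that follows has "treatment (FACT or AMBIT) as independent variable".

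**The two programmes (2.5.1.1, 2.5.1.2).** The standard AMBIT informed-MBT programme includes group therapy one to three times a week and a weekly individual session, over 18 months. In contrast, "MBT group-therapy is not mandatory in the AMBIT-PD condition", and treatment there averages three to five years.

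**Where they are delivered (2.2, 2.2.2).** There are 40 AMBIT informed-MBT patients, all from one team at Rivierduinen, and 40 AMBIT-PD patients, all from Altrecht, which has five such teams.

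**The concern.** The study is not randomised. Section 3.1.2 itself says that pre-treatment characteristics partly determine which treatment is indicated and may be related to outcome. The plan acts on this for AMBIT versus FACT but writes nothing comparable for the two AMBIT types. If the two groups differ at baseline in characteristics that predict how much the OQ-45.2 changes, that difference becomes part of the estimated contrast and could be reported as one form of AMBIT working better than the other.

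The contrast is secondary, but it is not incidental. The design section describes three settings, the sample size is calculated for three conditions, and the opening of the Discussion names both AMBIT types in the study aim. The characteristics needed for adjustment are already to be collected for the propensity score.

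**Working it through.** The plan gives no figure for this contrast, so there is none to reproduce. The check has four steps.

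**1. Does the stated matching cover this contrast?** It does not. Take a characteristic with mean 0 in FACT, +0.25 SD in one AMBIT group and −0.25 SD in the other, with 40 patients in each AMBIT group.
- Pooled AMBIT mean = (40 × 0.25 + 40 × (−0.25)) / 80 = 0, so AMBIT and FACT are perfectly balanced on it.
- Difference between the AMBIT groups = 0.25 − (−0.25) = 0.50 SD.

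Balance in the first contrast therefore says nothing about the second.

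**2. How large could the effect of unadjusted case mix be?**
- Group size: 40 v 40 (section 2.2), or 40 × 0.80 = 32 v 32 after the 20% dropout of section 2.2.1.
- Assumed, not in the documents: a standardised imbalance *s* in one characteristic and a correlation *r* of that characteristic with outcome change.
- Bias in SD units = *s* × *r*.
- SE = √(2/n), which is 0.224 for n = 40 and 0.250 for n = 32.
- Probability of rejecting at two-sided 5% with no true difference = Φ(bias/SE − 1.96) + Φ(−bias/SE − 1.96).

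| *s* | *r* | Bias (SD) | Rejection, 40 v 40 | Rejection, 32 v 32 |
|---|---|---|---|---|
| 0.3 | 0.3 | 0.09 | 6.9% | 6.5% |
| 0.5 | 0.4 | 0.20 | 14.5% | 12.6% |
| 0.8 | 0.5 | 0.40 | 43% | 36% |

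For the middle row at n = 40: 0.20/0.224 = 0.894, and Φ(−1.066) + Φ(−2.854) = 0.143 + 0.002 = 0.145. This treats the comparison as a single contrast of two means, not as the full repeated-measures model.

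**3. Can adjustment isolate AMBIT type?** It cannot. Among the 80 AMBIT patients, code type as 1 for AMBIT informed-MBT and 0 for AMBIT-PD, and site as 1 for Rivierduinen and 0 for Altrecht. The two columns are identical, and a design with intercept, type and site has rank 2 of 3. A propensity score for type is then also a model of which institution the patient attends. It can balance measured characteristics, but it cannot separate type from site, team or referral pattern. The exploratory moderation by location in 3.1.4 does not change this.

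**4. How much precision is there to spend?** The difference detectable with 80% power at a single time point is (1.96 + 0.84) × √(2/n), which is 0.63 SD at 40 v 40 and 0.70 SD at 32 v 32. That leaves little room for variable weights or a long covariate list.

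**The case against.** **The finding may rest on silence.** Section 3.2 does not say that the comparison is unadjusted. The primary model in 3.1.3 is written in the same shorthand and also lists no covariates, and a covariate list is often left to a fuller document. This has weight. The difference is that the primary model follows two subsections on matching for its own contrast, while those subsections confine their scope to AMBIT versus FACT. As written, the AMBIT-type contrast has no counterpart.

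**A reader might infer that the model contains nothing but type, so that any baseline difference in OQ-45.2 becomes a treatment effect.** The text does not support that. All three waves are outcomes, and a wave-by-type term, though not stated, is not ruled out. It would separate baseline level from change. What remains is imbalance in characteristics that predict change itself, and the concern is limited to that.

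**A reader might infer that patients are selected into one AMBIT type rather than the other by indication.** No section describes such a choice; the institution decides which type is available. Indication operates within each site, between AMBIT and FACT. Case mix can still differ between the two groups, through the different programme demands or local referral, but the article reports no such difference, and all participants meet the same criteria, including GAF ≤ 50. The programme contrast is itself not cleanly described: the sentence in 2.5.1.2 after the one quoted attributes individualised choice, including of group therapy, to AMBIT informed-MBT. That does not sit with 2.5.1.1 and needs reconciling.

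**Adjustment does not rescue the comparison as an estimate of AMBIT type.** This objection stands in full and shapes the fix.

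**The contrast is secondary, and the limitations section admits confounding.** True. None of the hypotheses in the Introduction concerns AMBIT type. That limits the importance of the point, but a general caveat does not replace an inexpensive adjustment with data already collected.

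**Conclusion.** The point holds in a limited form. As written, the comparison of AMBIT informed-MBT with AMBIT-PD has AMBIT type as its only named independent variable, and the confounding control elsewhere is built for a different contrast. Measured case mix that predicts change would enter the estimate unadjusted. The size, 0.09 to 0.40 SD of bias and a false-positive rate of about 6.5% to 43%, is an illustration. It rests on assumed imbalances and correlations, and its upper end needs the most extreme combination at 40 v 40. It is not a forecast.

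A reader might conclude that a propensity step of its own would turn this into a valid estimate of AMBIT type. The documents do not support that, because type and institution coincide completely. Adjustment removes measured case mix and no more. The change should be made, but it concerns a secondary comparison and does not touch the primary AMBIT versus FACT analysis.

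**What to change.** In section 3.2:

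1. State that the AMBIT-type comparison uses all AMBIT participants, not only those matched to a FACT patient.
2. State that the comparison is read from the wave-by-type term, so that baseline OQ-45.2 level is separated from change.
3. Adjust for the pre-treatment characteristics of 3.1.2. With about 40 patients per group, a small set of covariates chosen in advance is preferable. Enter each with its interaction with wave, because T0 is an outcome and a covariate main effect alone adjusts level rather than change. A separate propensity weight for AMBIT informed-MBT versus AMBIT-PD is the alternative.
4. State that the adjustment is partial, because each type is delivered at one institution only, and report the result as a descriptive programme-plus-site comparison, not as an effect of AMBIT type.

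The cost is a little more analysis of data already being collected, and some loss of precision if weights are used. Unmeasured differences, and everything that goes with the institution, remain.
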